## Abstract

**Background:**

Skin-to-skin contact (SSC) is an evidence-based intervention that benefits low birth weight /preterm infants. However, China’s health institutional policy inhibits parents from visiting their baby in the neonatal intensive care unit (NICU). In addition, the Chinese traditional postpartum behavioral practice of confining women to home raises barriers to mother-infant contact. Thus, to shorten the duration of parent-infant separation, father-infant SSC is considered a possible alternative. This study determines whether it is safe to perform father-infant SSC in the NICU and investigates how paternal SSC affects outcomes compared with traditional care (TC) for moderately preterm infants.

**Methods/design:**

A randomized controlled trial will be used to investigate the effects of paternal-infant SSC in NICU wards in China. Preterm infants born at a gestational age in the range of 32^0^–34^6^ weeks with a birth weight > 1500 g will be eligible. A simple random sampling method will be used to allocate infants to the SSC group (*n* = 25) or the TC group (*n* = 25). After medical stability, infants in the SSC group will be provided SSC by fathers for one hour every day until discharged from hospital. The primary outcome is neurodevelopmental measures, specifically salivary cortisol and Premature Infant Pain Profile (PIPP) during hospitalization. At 40 weeks of corrected age, infants will be assessed using the Infant Neurological International Battery (INFANIB) and neuroimaging. Secondary outcomes include infants’ physiological stability during SSC and throughout hospitalization and state observation at discharge. The fathers’ mental health will be assessed with the State-Trait Anxiety Inventory (STAI) 1 day to 3 days after the infant’s admission to the NICU and at discharge. Father-infant attachment will be evaluated at 4 and 6 months after the infants’ discharge, measured by the Paternal Postnatal Attachment Scale (PPAS). Statistical analyses will be conducted using a two-sided significance level of 0.05.

**Discussion:**

The effects of paternal-infant SSC on moderately preterm infants will be assessed. The data gathered in this study may have important implications for medical practice and policy in the NICU regarding the care methods of premature infants in China.

**Trial registration:**

Chinese Clinical Trial Registry, ChiCTR-IOR-1701274. Registered on 20 September 2017. Retrospectively registered.

**Electronic supplementary material:**

The online version of this article (10.1186/s13063-018-3060-2) contains supplementary material, which is available to authorized users.

## Background

Every year, approximately 15 million babies are born preterm (gestational age (GA) less than 37 weeks), and more than 60% of these preterm births occur in Africa and South Asia [1]. China ranks second in the top 10 countries with the greatest number of preterm deliveries [2]. According to the National Health and Family Planning Commission of the People’s Republic of China, preterm births account for approximately 7.0% of the total births in China, and they are the main cause of infant mortality [3]. Although the survival rate of preterm infants has increased because of the recent advances in neonatal care, premature births can cause varying degrees of adverse long-term neurodevelopmental impairment, which burdens both the family and country [4].

Preterm birth interrupts the normal process of brain maturation, putting infants at great risk of neurodevelopmental vulnerability and fragility [5]. During the third trimester, brain volume increases approximately 2.7-fold from 29 to 41 weeks postconception, which means that very preterm infants have a significantly smaller total brain volume than their term-born peers [6]. These reductions persist throughout childhood and adolescence [7]. Regional brain volumes near term are a promising marker for predicting disturbances in cognitive and behavioral outcomes in preterm infants [8]. Moreover, newborns must be exposed to the extrauterine environment in the neonatal intensive care unit (NICU) while the immature preterm brain is not yet ready to process various stimuli, including lights, noise, and painful interventions [9]. The infants’ sensory experience before term may cause negative effects on brain development and alter brain function and structure [10, 11].

Among those adverse stimuli, painful invasive procedures are the prominent experience that infants must undergo within the context of the NICU. Evidence shows that preterm infants experience a median of 10 painful procedures per day during hospitalization, 79.2% of which occur without specific analgesia [12, 13]. Unrelieved repeated pain exposure is associated with subsequent alterations in pain sensitivity, which may result in deleterious consequences including emotional, behavioral, and learning disabilities [14].

Nevertheless, preterm infants’ developmental outcomes appear to be modified by improving the NICU environmental experience and providing neuroprotective caregiving practices, as supported by the concept that the young brain has the ability of neuroplastic response [9]. This considerable plasticity of the brain can be expected at approximately 3 months before term age [15]. These critical and sensitive periods of brain development can create “windows of opportunity” for NICU-based interventions that may be beneficial for neurodevelopment [16].

Skin-to-skin contact, also known as kangaroo care (KC), is one of the recommended interventions to improve preterm birth outcomes according to the WHO [17]. SSC is globally accepted under different circumstances. In low-income settings, SSC is ideally provided for 24 h/day as a health care strategy; in affluent settings, SSC is considered an alternative option to shorten the length of parent-infant separation [18]. Regardless of how SSC is applied, multiple lines of evidence have suggested the short-term benefits of SSC for preterm infants. SSC has been used as a pain treatment to attenuate behavioral responses as well as to decrease cortisol levels. Studies found that Premature Infant Pain Profile (PIPP, a behavioral measure of pain for premature infants) scores and salivary and serum cortisol were lower on response to heel sticks in preterm infants who received SSC than in those who were treated with incubator care [19, 20].

Furthermore, infants who received SSC were found to have more organized sleep patterns, with longer periods in the alert wakefulness and quiet sleep states [21]. SSC infants showed a more mature neurodevelopmental profile [21, 22] and scored higher on the Bayley Scales of Infant Development and Psychomotor Developmental Index at 6 months [23]. In addition to these existing behavioral sleep findings, more rigorous neurophysiologic results measured by electroencephalographic/polysomnographic records also demonstrated that fewer rapid eye movements, more quiet sleep, and lower arousal were noted in SSC preterm infants than in the control cohort [24, 25], indicating the effect of SSC on improving sleep organization and accelerating brain maturation. Because sleep is vital for normal development, SSC may be used as an intervention to promote better sleep patterns within the context of the NICU environment. In addition to the above benefits, it is acknowledged that SSC helps establish parent-infant attachment.

According to the regulation theory of Schore [26], early maternal-infant separation can pose risk on attachment patterns, which is associated with alterations in brain structure and function. Research showed that very low birth weight (LBW) preterm infants with neurological impairment were more likely to develop an insecure quality of attachment [27]. Maternal-infant interactions were less synchronous at 3 months [28], and mothers of preterm infants were more likely to suffer from psychiatric illness (depression, anxiety) [29], which contributed to adverse attachment outcomes [30]. The physical closeness and sensory stimulations of SSC play an important role in regulating maternal-infant interaction. Evidence demonstrates that SSC can attenuate the negative psychological effects of premature birth by enhancing mothers’ sense of competence and sensitivity towards their infants, by decreasing mothers’ stress scores and increasing maternal-infant attachment scores [31–33], and by facilitating a better maternal-infant interactive style [34, 35].

Although it remains unclear whether SSC has long-lasting effects on preterm infants in terms of neurodevelopmental outcomes, studies show that KC may have a direct effect on infant neurophysiological organization [23]. Long-term follow-up studies have found that KC preterm infants show attenuated stress responses, have organized sleep and better cognitive control, and maintain long-lasting social and behavioral protective effects even after 10 and 20 years [36, 37].

KC has been recognized as an evidence-based intervention to improve health outcomes for LBW/preterm infants; however, it is not common in China. According to the national policy in China, parents are not allowed to enter the NICU to stay with their infants. Parent-infant separation begins after delivery until the infant is discharged, which accounts for a long period of time. This model of NICU care is accepted because it avoids the incidence of infection and also because of the ease of managing the patients. For severely ill infants, one of the preventive measures is to reduce the incidence of infection, which should be addressed by professionals. However, for medically stable preterm infants, a meta-analysis showed that LBW infants who received KC had reduced incidence of mortality, nosocomial infection, and severe illness compared to those who did not receive KC [38]. These results also support the idea that parents entering the NICU wards did not increase the risk of LBW infants becoming infected [38, 39]. Furthermore, the concept of family-centered care (FCC), which allows parents to participate in taking care of the baby, has been increasingly considered an important component of the NICU [40]. Evidence shows that FCC is feasible and safe, and it does not increase the rates of nosocomial infection; the incidence of necrotizing enterocolitis (NEC) was significantly lower in the FCC group in previous studies [41, 42]. These results indicate that allowing parents to visit their infants and perform SSC with adequate hygiene practice is safe, and it could be applied in Chinese NICUs.

According to the definition of KC, the mother is the optimal provider for SSC, to promote breastfeeding. However, in China, women are encouraged to stay at home and to rest completely for 1 month after birth (called “doing the month”) for recovery [43]. These traditional postpartum practices are accepted regardless of a woman’s age and education [44]. This resting period results in mothers not being able to perform even one or a few hours’ session of SSC per day after discharge from the hospital, which will greatly delay mother-infant exposure in the first month. In this case, father-infant SSC is an optimal alternative.

Whereas most studies focus on the effects of maternal-infant SSC, few studies have researched the father’s participation in SSC. Ludington-Hoe et al. and Erlandsson et al. found that infants who received father-infant SSC maintained higher skin temperature and had better state behavior responses [45, 46]. In addition, no negative effects were observed on the metabolic rate and energy balance in performing paternal SSC [47, 48]. Evidence also suggested that, to some extent, father-infant SSC was capable of decreasing pain response in preterm infants [49–51]. Infants who received KC cried less, and fathers communicated more vocally not only with the newborn but with the mother. Fathers who provided SSC were more willing to be involved in infant care [52], which established bonding and attachment [53] with the infant and created a more stimulating, more harmonious, and generally better family environment [54] beneficial for infant development [23]. Qualitative studies also reported that fathers felt grateful for being needed; they also felt more included in the process, which facilitated their attainment of a paternal role and achievement of equal parenthood [55–58].

As mentioned previously, premature birth can be stressful and traumatic for parents and can cause negative consequences for the natural establishment of the parent-infant relationship. The NICU environment interrupts parental involvement in caring for the infant and jeopardizes the process of attachment between parents and infant. It is recognized that fathers play an important role in the care of their children. Positive father-child interactions established at an early age have been shown to reduce cognitive delay in infants [59]. A father’s involvement is associated with improved cognitive outcomes in preterm infants, which may suggest a possible intervention [60]. Studies show that fathers of preterm infants often feel stressed [61], overwhelmed, isolated, and out of control [62]. Parental psychological well-being and parent-child interaction may affect infants’ development outcomes. However, these negative feelings appeared to be relieved by offering SSC, as fathers reported feeling in control and at ease when they were more involved in caring for their infants. By providing SSC, fathers consider themselves an important part in the course of caring for infants through physical closeness [55].

The aim of the present study is to investigate whether paternal SSC is safe and how it affects outcomes for moderately preterm infants born at GA 32^0^–34^6^ weeks. We hypothesize that the practice of father-infant SSC in the NICU is feasible and will benefit both infants’ and fathers’ well-being.

## Objectives

### Primary objective

The primary objective of this trial is to study the effect of early paternal SSC versus traditional care (TC) on neurodevelopmental outcomes measured by salivary cortisol, the PIPP, the Infant Neurological International Battery (INFANIB), and neuroimaging.

### Secondary objectivesThe secondary objectives of the study are the following:

To assess the safety and physiological stability of father-infant SSCTo study the effect of father-infant SSC on infants’ state behaviorsTo investigate the effect of father-infant SSC on paternal psychological statusTo investigate the effect of father-infant SSC on father-infant attachment

## Methods

### Study design

This study is a randomized controlled, parallel-designed clinical trial. The infants in one group will receive 1-h paternal SSC, and the infants in the other group will receive no paternal SSC. We will recruit singleton and twin preterm infants with a GA of 32^0^–34^6^ weeks and with BW ≥ 1500 g delivered either vaginally or by C-section. Infants with unstable medical condition who are evaluated by a neonatal doctor will be excluded. The infants allocated to the TC group will receive standard care in an incubator during hospitalization. The infants in the intervention group will be offered father-infant SSC at least 1 h every day in addition to standard care. Further treatment during hospitalization will not differ between the groups. The flowchart for the study is shown in Fig. 1. The schedule of study enrollment, interventions, and assessments is given in Table 1.

**Fig. 1 Fig1:**
[figure not shown]
Flowchart of study design

**Table 1 Tab1:** Schedule of enrollment, interventions, and assessments

Time point	Study Period								
	Enrolment	Allocation	Post-allocation						
	*-t* _*1*_		*t* _*1*_	*t* _*2*_	*t* _*3*_	*t* _*4*_	*t* _*5*_	*t* _*6*_	*t* _*7*_
Enrolment:									
Eligibility screen	X								
Informed consent	X								
Randomization and allocation		X							
Interventions:									
SSC group			X						
TC group			X						
Assessments:									
State-Trait Anxiety Inventory, STAI				X		X			
Salivary cortisol					X				
Brazelton Neonatal Assessment Scale, BNAS						X			
Neuroimaging							X		
Infant Neurological International Battery, INFANIB							X		
Paternal Postnatal Attachment Scale, PPAS								X	X

t_1_ = During hospitalization

t_2_ = 1 day to 3 days after birth

t_3_ = 10-15 days after birth

t_4_ = 37 weeks of corrected age or before discharge

t_5_ = 38-42 weeks of corrected age

t_6_ = 4 months after discharge

t_7_ = 6 months after discharge

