### Trial treatments

All infants admitted to the NICU will be given parenteral nutrition, cared for under radiant warmers, and treated with further interventions according to the health status of the infants. After the initial stabilization, infants will be randomly assigned to either the SSC group or the TC group according to randomization and allocation rules.

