### Intervention group

Infants in the intervention group will be offered SSC as soon as they are stable (approved by a pediatrician in the unit), and they are expected to receive SSC every day during hospitalization. SSC will be performed between 4:00 pm and 6:00 pm for at least 1 h in a private room adjacent to the unit with an ambient temperature between 22 and 24 °C and appropriate light and sound levels. Fathers will wear a comfortable gown and be seated on a reclining chair at an angle of 40 to 60°. Each infant will be taken out of the incubator, unclothed (only diaper and cap are kept on), and placed in an upright position on the father’s chest. The infants will be covered by a blanket to keep them warm. Fathers will be educated on how to hold the infant correctly and encouraged to watch their child and talk to them. Father and baby will be left in the kangaroo position for at least 1 h. During SSC, infants will remain attached to a cardiorespiratory monitor and will be observed by a nurse; routine nursing including parenteral nutrition administration and IV injection can also be performed. Because SSC is not routine care in our hospital, this practice will follow the World Health Orgainization (WHO) guidelines [63].

If hypothermia or apnea of any duration accompanied by desaturation occurs during the SSC, the intervention will be discontinued, and the eligibility of the infant will be reassessed. Infants in the intervention group will receive the same standard treatment as infants in the TC group except for at least 1 h of SSC every day.

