#### Fathers’ mental status

The State-Trait Anxiety Inventory (STAI) will be used to assess fathers’ mental status in regard to state and trait anxiety [71]. The questionnaire consists of two parts, each containing 20 statements. One part assesses state anxiety, and the other part assesses trait anxiety. This questionnaire was translated into a Chinese version in 1988, and the internal consistency reliability was 0.95 [72, 73]. All items are scored according to a 4-point Likert scale. Two parts are calculated, with a minimum score of 20 and a maximum score of 80. Higher scores indicate higher levels of anxiety.

Fathers will complete this questionnaire at the following time points: (1) 1 day to 3 days after the infant’s birth and (2) when the infant is discharged from the NICU.

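### No anxiety score taken before allocation is assured: Table 1 puts the first paternal STAI after allocation, and the text does not fix the order of STAI, allocation and first SSC session

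*Protocol article*

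**What the plan says.** Table 1 (Schedule of enrollment, interventions, and assessments) marks the STAI at t2 and t4, both under the post-allocation heading. It defines t2 as "1 day to 3 days after birth". Both arms' interventions are marked at t1, defined as "During hospitalization". The Enrolment column holds only the eligibility screen and consent, so no STAI is scheduled before allocation.

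The section on fathers' mental status gives the two time points as "1 day to 3 days after the infant’s birth and (2) when the infant is discharged from the NICU". The abstract counts the first one from a different origin: "1 day to 3 days after the infant’s admission to the NICU and at discharge".

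On the order of events, Trial treatments states: "After the initial stabilization, infants will be randomly assigned to either the SSC group or the TC group". The inclusion criteria require 24 to 72 hours of stable vital signs. The Intervention group section adds: "Infants in the intervention group will be offered SSC as soon as they are stable".

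Fathers in the SSC arm deliver the intervention themselves ("Fathers will be educated on how to hold the infant correctly"), and infants in the control arm get no paternal SSC. Data analysis names the independent t test and repeated measures ANCOVA for continuous variables as a class. It names no covariate and does not say which method is meant for the STAI.

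**The concern.** A score that serves as the starting point of a change analysis, or as a covariate, should be measured before anything that differs between the arms can influence it. The first STAI is not protected in this way. A father who has been told that he will hold his infant, or that he will not, may answer the state-anxiety items differently, and one who has already had a session may do so even more. If such a score is subtracted or adjusted for, part of the treatment effect is subtracted or adjusted for with it. The score would also mean different things for different fathers: untouched by allocation for some, after allocation for others.

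The effect on paternal psychological status is one of the stated secondary objectives. A pre-allocation score that was never collected cannot be recovered later by any analysis plan, so the point belongs to the schedule and not only to the analysis.

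**Working it through.** **Plan's own figure.** The article gives no figure for the STAI. Its only sample size concerns salivary cortisol. The difference is 0.57 − 0.21 = 0.36 and the pooled SD is √((0.12² + 0.61²)/2) = 0.4396, so d = 0.819. At two-sided 5% and 80% power the noncentral t gives 24.4, rounded up to 25 per group. The stated number reproduces, but it does not bear on this point.

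**Order of events.** Let stability begin s hours after birth and be required for h hours, with h between 24 and 72. Allocation then comes no earlier than s + h. Read the STAI window as 24 to 72 hours after birth.

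| s | h | Earliest allocation | Relation to the first STAI |
|---|---|---|---|
| 0 | 24 | 24 h | STAI may follow allocation by up to 48 h |
| 24 | 24 | 48 h | either order |
| 0 | 72 | 72 h | STAI comes first, or coincides |
| 24 | 72 | 96 h | STAI comes first |

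In the first row, up to two of the daily afternoon sessions could take place before a father answers at 72 hours. In the last two rows, following the text means that the STAI is answered before allocation, contrary to its column in Table 1. No section states which event comes first.

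**Effect on the estimate.** Let D be the true difference at discharge, f the share of D already present in the first score, and r the within-arm correlation of the two scores, with equal SDs.

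- Discharge score alone: expected estimate D.
- Change score: D − f·D = D(1 − f).
- ANCOVA on the first score: D − r·f·D = D(1 − r·f).

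The documents give neither f nor r. Over assumed ranges:

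| f | Change keeps | ANCOVA keeps (r = 0.7 to 0.3) |
|---|---|---|
| 0 | 100% | 100% |
| 0.10 | 90% | 93% to 97% |
| 0.25 | 75% | 82.5% to 92.5% |
| 0.50 | 50% | 65% to 85% |

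If the early shift runs against the later effect, f is negative and the estimate is inflated. At f = −0.25, change gives 125% of D and ANCOVA gives 107.5% (r = 0.3) to 117.5% (r = 0.7).

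**Illustration by simulation**, with assumed D = 0.8 SD, r = 0.5 and 25 fathers per arm (twins ignored). The ANCOVA estimate is 0.80 with power about 0.89 at f = 0; 0.70 with power about 0.79 at f = 0.25; and 0.60 with power about 0.65 at f = 0.50. The simulated estimates agree with the formula.

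**The case against.** A reader might infer that the trial adjusts for a contaminated baseline. The article does not say so. It uses the word baseline only for the saliva sample before the heel stick, assigns no method to the STAI and names no covariate. Such detail is commonly left to an analysis plan, which is not shown. If the t test it names is applied to discharge scores, no bias arises. This objection stands, and it makes the concern conditional on a change, repeated-measures or adjusted analysis. Two time points together with a planned repeated measures ANCOVA make such an analysis plausible.

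A reader might also infer that every father answers after allocation and knowing his arm. Table 1 read alone says the former, but its columns are not strictly chronological, since t1 spans the whole stay. The stability criterion lets some fathers, perhaps many, answer first. The article does not say when fathers are told. This stands too: what is supported is that the order is not fixed.

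Thirdly, a reader might take the percentages as the size of the bias. They follow directly from the assumed f and r. A large f is hard to defend after at most two sessions, and the sign is open: relief could lower the first score, while anticipation or disappointment could move it the other way. The argument also concerns the state part of the STAI more than the trait part.

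What the objections do not remove is that Table 1 schedules no STAI before allocation and that no section secures one.

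**Conclusion.** The point holds in a limited form. The schedule does not assure a pre-allocation anxiety score, and the sections on timing allow allocation and possibly a first SSC session to fall on either side of the first STAI. Any analysis that uses that score as an origin or covariate is open to bias of unknown direction and size. The working shows only how an assumed contamination would carry through. A between-arm comparison of discharge scores is unaffected.

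This touches one secondary outcome and none of the primary measures, and the planned 50 infants need not change. It is worth correcting because the remedy is cheap and recruitment was still under way.

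Separately, the abstract counts the first STAI from NICU admission, while Table 1 and the outcome section count it from birth. All infants are born in the study hospital, so the gap may be short, but the article does not state it and the passages need reconciling.

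**What to change.** - Have the father complete the first STAI after consent and before the allocation envelope is opened, and move it to the Enrolment column of Table 1.
- State the same time point in the abstract, in Table 1 and in the section on fathers' mental status.
- For fathers already enrolled, record whether the first STAI preceded allocation. If for many it did not, make the between-arm comparison of discharge scores the main STAI analysis, and show the analysis adjusted for pre-allocation scores as supportive.

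The cost is small: an online questionnaire already in use is reordered, and staff check that it is complete before opening the envelope. The downside is that some enrolled fathers will have no usable pre-allocation score. Those missing scores will tend to belong to infants who stabilized early, and the adjusted analysis will be less precise. This is why it should be supportive and not the main analysis if many scores are lost.

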## Outcome measures

### Primary outcome measure

The primary outcome is the neurodevelopmental outcomes of preterm infants, which will be measured by salivary cortisol and PIPP during hospitalization (at the age of 10–15 days) and by INFANIB and neuroimaging at term-equivalent age (40 weeks of corrected age).

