#### Infant Neurological International Battery

The INFANIB is used as a screening tool to assess infants’ neurodevelopmental status at term-equivalent age (40 weeks of corrected age). This instrument was established by Ellison and Browning in 1985 and was designed to detect gross motor developmental delay and, it was hoped, to predict later neurological dysfunction during the first 18 months of life [66]. Evidence shows that the INFANIB is an appropriate neurological outcome test for premature and/or LBW infants [67–69].

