#### Magnetic Resonance Imaging (MRI)

Quantitative MRI will be used to observe preterm infants’ brain growth at term-equivalent age. Total cerebral volume, volumes of white and gray matter, and the cerebral cortex will be measured to predict brain development in preterm infants.

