### Data analysis

The data analysis will be conducted on an intention-to-treat basis. All the study subjects will be analyzed in the groups into which they were originally randomized.

Descriptive characteristics will be analyzed using frequencies and percentages. The independent *t* test and a repeated measures analysis of covariance (RM-ANCOVA) will be used to compare differences between the two groups for continuous variables. Categorical variables will be compared using the Pearson chi-square test or Fisher’s exact test. *P* values less than 0.05 will be considered significant. Data will be analyzed using the statistical software SPSS 23.0 (IBM SPSS Statistics, IBM Corporation, Armonk, NY, USA).

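### Brain volumes are dated to 40 weeks in the text but 38–42 weeks in Table 1, and the t test that would apply to them ignores age at scan, which costs precision

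*Protocol article*

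**What the plan says.** Three places in the Protocol article give a single age:

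- Abstract, Methods/design: "At 40 weeks of corrected age, infants will be assessed using the Infant Neurological International Battery (INFANIB) and neuroimaging".
- Primary outcome measure: "by INFANIB and neuroimaging at term-equivalent age (40 weeks of corrected age").
- The INFANIB section, for that instrument: "assess infants’ neurodevelopmental status at term-equivalent age (40 weeks of corrected age").

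Table 1 marks neuroimaging and INFANIB once each, at t5, which its footnote defines as "38-42 weeks of corrected age".

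The MRI endpoint consists of absolute volumes: "Total cerebral volume, volumes of white and gray matter, and the cerebral cortex will be measured". The Background says that in the third trimester "brain volume increases approximately 2.7-fold from 29 to 41 weeks postconception".

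Under Data analysis, the independent t test is named first, and then "a repeated measures analysis of covariance (RM-ANCOVA) will be used to compare differences between the two groups for continuous variables". No covariate is named for any outcome, and no test is assigned to a particular outcome.

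**The concern.** Neuroimaging and INFANIB are both listed components of the primary outcome, and their age of assessment is stated in two ways. A reader following Table 1 could scan an infant two weeks either side of the age in the outcome definition.

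For brain volume this is more than a labelling matter, because the protocol itself says the brain is growing fast at this stage. RM-ANCOVA needs repeated measurements and each volume is measured once. That leaves the independent t test, which cannot take age at scan into account. Volume differences that merely reflect scan date then stay in the error term. At stake is power for a primary component in a trial of 50 infants whose size was set on salivary cortisol alone.

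**Working it through.** **The plan's own sample size.** The cortisol inputs under Sample size are 0.21 (SD 0.12) and 0.57 (SD 0.61). Pooled SD = √((0.12² + 0.61²)/2) = 0.440, so d = 0.36/0.440 = 0.819. For a two-sided 5% t test with 80% power this needs 24.4, rounded up to 25 per group (power 0.81 at 25). The stated size reproduces. At 25 per arm, the difference detectable with 80% power is 0.809 SD, and this is the benchmark below. The protocol gives no effect size or power for MRI.

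**Growth rate from the Background figure.** Read 2.7-fold as a ratio of 2.7 over 12 weeks, with volume at 29 weeks set to 1.

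- Exponential: 2.7^(1/12) − 1 = 8.6% per week. From 38 to 42 weeks: 2.7^(4/12) − 1 = 39%.
- Linear: slope 1.7/12 = 0.1417 per week; volume at 40 weeks is 1 + 11 × 0.1417 = 2.558; 0.1417/2.558 = 5.5% of the week-40 volume per week. From 38 to 42 weeks: 2.842/2.275 − 1 = 25%.

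**Spread of scan ages (assumed; not in the document).** Three cases:

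- uniform over the four weeks, SD = 4/√12 = 1.15 weeks;
- triangular, peaking at 40 weeks, SD = 2/√6 = 0.82 week;
- clustered near 40 weeks, SD 0.5 week.

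Multiplying by the weekly growth gives the SD in volume due to age alone: 6.4–10.0% (uniform), 4.5–7.1% (triangular) and 2.8–4.3% (clustered).

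**Effect on power.** Let CV be the coefficient of variation between infants of the same age (also assumed). The unadjusted SD is √(CV² + age SD²). With CV 10% and uniform ages this is √(10² + 6.39²) = 11.9% to √(10² + 9.96²) = 14.1%, so the variance is 1.4 to 2.0 times as large. The difference detectable with 80% power rises from 0.809 × 10% = 8.1% to 9.6–11.4%.

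Unadjusted power for an effect that would have 80% power at a fixed age (exponential to linear growth):

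| Scan ages | CV 5% | CV 10% | CV 15% |
|---|---|---|---|
| Uniform over 38–42 weeks | 24–41% | 51–66% | 65–73% |
| Triangular about 40 weeks | 37–55% | 63–72% | 72–76% |
| Clustered, SD 0.5 week | 56–69% | 73–77% | 77–79% |

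The growth figure is an average over 29–41 weeks. The calculation applies it as a local rate and carries it one week beyond that range.

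**The case against.** The strongest reply has three parts.

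First, 38–42 is centred on 40, so the text may be giving a nominal target and the table its visit window. That is a fair reading and makes the conflict mild. However, no section says so, and the analysis question remains even if it is accepted.

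Second, the protocol does not say that the volume comparison will be unadjusted. The data analysis section neither names age at scan as a covariate nor rules it out, and an analysis plan that is not shown may add it. This stands as a caveat. But of the two methods the article does state, the one that fits a single measurement has no place for a covariate.

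Third, the size of the loss rests on assumed inputs. This stands too. If scans cluster near 40 weeks and infants of equal age differ by 10–15%, the loss is only a few percentage points of power.

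A reader might also infer stronger conclusions, which the documents do not support:

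- *That scan age swamps any volume effect, or is the dominant source of variance.* With CV 10% and uniform ages, age accounts for 29–50% of the variance, and differences of about 10–11% remain detectable with 80% power.
- *That the comparison is biased.* Nothing suggests that families in one arm return sooner. Under randomisation, scan-age variation is noise, and chance imbalance is already reflected in the t test's standard error.
- *That the same figures hold for INFANIB, for white matter, gray matter or cortex separately, or for the state observation at discharge.* The Background figure is for brain volume as a whole and gives no number for any of these.

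**Conclusion.** The point holds as an inconsistency in timing together with an avoidable loss of precision. It does not show that the MRI comparison is invalid.

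The two timing statements are plain in the text, and growth of about 5.5–8.6% per week follows from the protocol's own figure, subject to the assumed growth shape. The loss itself is conditional. At a 10% between-infant CV with 25 per arm, power falls from 80% to about 51–66% with uniform scan ages, or to 73–77% with scans clustered near 40 weeks. At CV 5% and 15% with uniform ages it falls to 24–41% and 65–73%. The scan-age spread and the CV are both assumptions, so no single figure should be quoted as the cost. For INFANIB the point is qualitative only.

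**What to change.** 1. Analyse each MRI volume by ANCOVA, with the volume as outcome and group and exact postmenstrual age at scan (in days) as terms, in place of the independent t test. Specify this before the data are analysed. Age at scan is known only after randomisation, so report it by arm; comparing volumes at equal age is nonetheless what the outcome definition intends.
2. Apply the same model to INFANIB as an option, noting that the document does not quantify how its scores depend on age.
3. Make the abstract, the primary outcome section, the INFANIB section and Table 1 agree, for example by stating a 40-week target with a 38–42 week window.

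The cost is one degree of freedom per model and a text edit. Age at scan follows from gestational age at birth and the scan date, so no new data collection is needed.
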